#### **10.1.5. Assessment of severity**

Assessment of severity is one of the responsibilities of the investigator in the evaluation of AEs and SAEs. Severity will be graded according to <<the NCI CTCAE v4.03. The determination of severity for all other events not listed in the CTCAE should be made by the investigator based upon medical judgment and the severity categories of Grade 1 to 5 as defined below:

|                            |                                                                                                                                                                                                                                                                |
|----------------------------|----------------------------------------------------------------------------------------------------------------------------------------------------------------------------------------------------------------------------------------------------------------|
| Grade 1 (mild)             | An event that is usually transient and may require only minimal treatment or therapeutic intervention. The event does not generally interfere with usual activities of daily living.                                                                           |
| Grade 2 (moderate)         | An event that is usually alleviated with additional specific therapeutic intervention. The event interferes with usual activities of daily living, causing discomfort but poses no significant or permanent risk of harm to the subject.                       |
| Grade 3 (severe)           | An event that requires intensive therapeutic intervention. The event interrupts usual activities of daily living, or significantly affects the clinical status of the subject.                                                                                 |
| Grade 4 (life threatening) | An event, and/or its immediate sequelae, that is associated with an imminent risk of death or with physical or mental disabilities that affect or limit the ability of the subject to perform activities of daily living (eating, ambulation, toileting, etc). |
| Grade 5 (fatal)            | Death (loss of life) as a result of an event.                                                                                                                                                                                                                  |

It is important to distinguish between serious criteria and severity of an AE. Severity is a measure of intensity whereas seriousness is defined by the criteria in Section 9.2.1. A Grade 3 AE need not

necessarily be considered an SAE. For example, a Grade 3 headache that persists for several hours may not meet the regulatory definition of an SAE and would be considered a nonserious event, whereas a Grade 2 seizure resulting in a hospital admission would be considered an SAE.

#### **10.1.6. Assessment of relationship**

##### **Relationship to Investigational Product**

The investigator is required to provide an assessment of relationship of AEs and SAEs to the investigational product.

- An event will be considered “not related” to use of the investigational product if any of the following tests are met:
- An unreasonable temporal relationship between administration of the investigational product and the onset of the event (eg, the event occurred either before, or too long after, administration of the investigational product for it to be considered product-related)
- A causal relationship between the investigational product and the event is biologically implausible (eg, death as a passenger in an automobile accident)
- A clearly more likely alternative explanation for the event is present (eg, typical adverse reaction to a concomitant drug and/or typical disease-related event)

Individual AE/SAE reports will be considered “related” to use of the investigational product if the “not related” criteria are not met. “Related” implies that the event is considered to be “associated with the use of the drug” meaning that there is “a reasonable possibility” that the event may have been caused by the product under investigation (ie, there are facts, evidence, or arguments to suggest possible causation).

##### **Relationship to Protocol Procedures**

The investigator is also required to provide an assessment of relationship of SAEs to protocol procedures on the SAE Report Form. This includes non-treatment emergent SAEs (ie, SAEs that occur prior to the administration of investigational product) as well as treatment emergent SAEs. A protocol-related SAE may occur as a result of a procedure or intervention required during the study (eg, blood collection, washout of an existing medication). The following guidelines should be used by investigators to assess the relationship of SAEs to the protocol: Protocol related: The event occurred due to a procedure/intervention that was described in the protocol for which there is no alternative etiology present in the subject’s medical record. Not protocol related: The event is related to an etiology other than the procedure/intervention that was described in the protocol (the alternative etiology must be documented in the study subject’s medical record).

## **10.2. Recording of adverse events and serious adverse events**

Adverse events will be recorded in the eCRF using a recognized medical term or diagnosis that accurately reflects the event. Adverse events will be assessed by the investigator for severity, relationship to the investigational product, possible etiologies, and whether the event meets criteria of an SAE and therefore requires immediate notification to AstraZeneca/MedImmune Patient Safety.

The following variables will be collected for each AE:

- AE (verbatim)
- The date when the AE started and stopped
- Changes in NCI CTCAE grade and the maximum CTC grade attained
- Whether the AE is serious or not
- Investigator causality rating against durvalumab (yes or no) <<and/or comparator/combination drug (yes/no)>>
- Action taken with regard to durvalumab /comparator/combination agent
- Outcome

In addition, the following variables will be collected for SAEs as applicable:

- Date AE met criteria for serious AE
- Date Investigator became aware of serious AE
- AE is serious due to criteria
- Date of hospitalization
- Date of discharge
- Probable cause of death
- Date of death
- Autopsy performed
- Description of AE
- Causality assessment in relation to Study procedure(s)
- Causality assessment in relation to FOLFOX

Events, which are unequivocally due to disease progression, should not be reported as an AE during the study.

#### **10.2.1. Study recording period and follow-up for adverse events and serious adverse events**

Adverse events and serious adverse events will be recorded from time of signature of informed consent, throughout the treatment period and including the follow-up period (90 days after the last dose of durvalumab + tremelimumab or until the initiation of alternative anticancer therapy).

During the course of the study all AEs and SAEs should be proactively followed up for each subject. Every effort should be made to obtain a resolution for all events, even if the events continue after discontinuation/study completion.

If a subject discontinues from treatment for reasons other than disease progression, and therefore continues to have tumor assessments, drug or procedure-related SAEs must be captured until the patient is considered to have confirmed PD and will have no further tumor assessments.

The investigator is responsible for following all SAEs until resolution, until the subject returns to baseline status, or until the condition has stabilized with the expectation that it will remain chronic, even if this extends beyond study participation.

## **Follow-up of unresolved adverse events**

Any AEs that are unresolved at the subject's last visit in the study are followed up by the investigator for as long as medically indicated, but without further recording in the eCRF. After 90 days, only subjects with ongoing investigational product-related SAEs will continue to be followed for safety.

AstraZeneca/MedImmune retains the right to request additional information for any subject with ongoing AE(s)/SAE(s) at the end of the study, if judged necessary.

## **Post study events**

After the subject has been permanently withdrawn from the study, there is no obligation for the investigator to actively report information on new AE or SAEs occurring in former study subjects after the 90-day safety follow-up period for patients treated with durvalumab + tremelimumab. However, if an investigator learns of any SAEs, including death, at any time after the subject has been permanently withdrawn from study, and he/she considers there is a reasonable possibility that the event is related to study treatment, the investigator should notify the study sponsor and AstraZeneca/MedImmune Drug Safety.

### **10.2.2. Reporting of serious adverse events**

All SAEs will be reported, whether or not considered causally related to the investigational product, or to the study procedure(s). The reporting period for SAEs is the period immediately following the time that written informed consent is obtained through 90 days after the last dose of durvalumab + tremelimumab or until the initiation of alternative anticancer therapy. The investigator and/or Sponsor are responsible for informing the Ethics Committee and/or the Regulatory Authority of the SAE as per local requirements.

#### **10.2.2.1. Reporting of deaths**

All deaths that occur during the study, or within the protocol-defined 90-day post-last dose of durvalumab + tremelimumab (or until the initiation of alternative anticancer therapy) safety follow-up period must be reported as follows:

- Death that is clearly the result of disease progression should be documented but should not be reported as an SAE.
- Where death is not due (or not clearly due) to progression of the disease under study, the AE causing the death must be reported to as a SAE within **24 hours** (see Section 10.3.2 for further details). The report should contain a comment regarding the co-involvement of progression of disease, if appropriate, and should assign main and contributory causes of death.
- Death with an unknown cause should always be reported as a SAE.
- Death that occur following the protocol-defined 90-day post-last-dose of MEDI4736 safety follow-up period will be documented <<as events for survival analysis>>, but will not be reported as an SAE.

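### After day 90, a treatment-related SAE or death must be captured under Section 10.2.1 but falls outside the SAE rules of Sections 10.2.2 and 10.2.2.1

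*Protocol*

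**What the plan says.** Five places in Section 10.2 of the Protocol govern events after day 90.

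- **Section 10.2.1, general window.** AEs and SAEs are recorded from consent to "90 days after the last dose of durvalumab + tremelimumab or until the initiation of alternative anticancer therapy".
- **Section 10.2.1, extension.** If a patient stops treatment for a reason other than progression, and so continues tumour assessments, "drug or procedure-related SAEs must be captured until the patient is considered to have confirmed PD and will have no further tumor assessments".
- **Section 10.2.1, Post study events.** After permanent withdrawal there is no duty of active reporting beyond the 90 days. However, "if an investigator learns of any SAEs, including death, at any time after the subject has been permanently withdrawn from study", and considers a link to treatment reasonably possible, "the investigator should notify the study sponsor and AstraZeneca/MedImmune Drug Safety".
- **Section 10.2.2.** SAEs are reportable whether or not they are related, from consent "through 90 days after the last dose of durvalumab + tremelimumab or until the initiation of alternative anticancer therapy".
- **Section 10.2.2.1, last bullet.** Deaths after the 90-day period "will be documented <<as events for survival analysis>>, but will not be reported as an SAE".

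Section 11.3.1 then plans the number and percentage of patients with at least one SAE.

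**The concern.** Section 10.2.1 on its own is coherent: a general window, then an exception that keeps related SAEs open for one defined group. Sections 10.2.2 and 10.2.2.1 restate the window and leave the exception out. Section 10.2.2.1 goes further and rules out SAE status for any later death, whatever its cause.

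The group covered by the exception includes patients who stop for toxicity without progressing. Section 9.4 provides for continued tumour assessments in patients withdrawn for reasons other than confirmed progression, so the group exists by design. Safety is the primary objective of the Phase Ib part, safety data continue to be collected in step 2, and Section 6.2.3 states that this combination has not been evaluated before. A related death that is filed only as a survival event would be absent from the SAE data on which the safety description rests.

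**Working it through.** No figure in the plan depends on this point, so there is nothing to reproduce. The check is to apply each rule to test cases. Assume an event on day 120 after the last dose and no new anticancer therapy.

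| Case | 10.2.1 extension | Post study events | 10.2.2 | 10.2.2.1, last bullet |
|---|---|---|---|---|
| A. Related non-fatal SAE; stopped without progression, still scanned | Capture | Not applicable until withdrawn from study | Outside the period | Not applicable |
| B. Related death; same patient | Capture | Not applicable unless already withdrawn | Outside the period | Survival event, not an SAE |
| C. Possibly related death; permanently withdrawn from study | Not applicable if stopped for progression or no longer scanned | Notify if learned of | Outside the period | Survival event, not an SAE |
| D. Unrelated death | Not required | Not required | Outside the period | Survival event, not an SAE |

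**Case A.** Sections 10.2.1 and 10.2.2 disagree. The first requires capture. The second has closed the period and does not refer to the extension.

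**Case B.** This is the sharpest conflict. Death is one of the seriousness criteria in Section 10.1.2, so a drug-related death is a drug-related SAE and must be captured under Section 10.2.1. Section 10.2.2.1 says it is not reported as one. A site cannot follow both.

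**Case C.** The post-study paragraph treats a possibly related death as an SAE to be notified. Section 10.2.2.1 denies it SAE status, with no exception.

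**Case D.** All the rules agree, so nothing needs to change for unrelated late deaths.

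**Consequence for the analysis.** Section 8.1.3 follows all patients for survival to the end of the study, so late deaths will become known. Whether a related one also appears in the SAE count of Section 11.3.1 depends on whether the site applied Section 10.2.1 or Sections 10.2.2 and 10.2.2.1.

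**The case against.** The best defence is that Section 10.2.2 and the post-study paragraph fit together: a fixed period of active reporting, followed by a safety valve for related events that come to light later. That reading is fair, and those two passages alone are not a contradiction. It does not settle cases A and B, because the post-study paragraph begins only at permanent withdrawal from the study and these patients are still in follow-up. Nor does it soften the unqualified last bullet of Section 10.2.2.1 in case C.

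The scope is also narrow. The extension covers only patients who stopped without progression and are still being scanned. The post-study wording is that the investigator should notify; it does not say that the event enters the eCRF or the tables. Both limits stand.

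A reader might infer more, in four ways that the Protocol does not support.

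- **Deaths of unknown cause.** Section 10.2.2.1 also says "Death with an unknown cause should always be reported as a SAE". This could be set against the last bullet. The bullets sit under a lead-in about deaths during the study or within the 90-day window, so the natural reading is that this one applies inside the window and the last one outside it.
- **FOLFOX-related SAEs.** The subsection on unresolved events says "After 90 days, only subjects with ongoing investigational product-related SAEs will continue to be followed for safety", and Table 9 in Section 15.1 omits FOLFOX. It does not follow that FOLFOX-related SAEs are lost. The title page, the synopsis and Section 5 list FOLFOX as investigational, and Section 10.2 requires an SAE causality assessment against it.
- **Ongoing SAEs.** The same sentence is narrower than Section 10.2.1, which follows all SAEs to resolution or stabilisation. An SAE that began inside the window is already recorded, so only the length of its follow-up is at stake.
- **A count of lost events.** One could apply the 26.5% AE discontinuation rate in Section 1.4.2.3 to 57 patients (57 × 0.265 = 15.1) and add a progression assumption. That gives patients at risk, not SAEs missed. The rate also comes from a lung cancer study without FOLFOX that pooled higher tremelimumab doses.

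**Conclusion.** The inconsistency is real and the text is wrong as written. The firm conflicts are the Section 10.2.1 extension against Section 10.2.2, and the extension together with the post-study paragraph against the last bullet of Section 10.2.2.1. A related SAE or death after day 90 can be captured under one passage and left out under another, so the SAE count in Section 11.3.1 can depend on which sentence a site follows.

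The size cannot be stated: the Protocol gives neither a rate nor a timing of late related events. The conclusion is that such events can be lost, not that they will be. It rests on the wording of the current text alone. A block of text between the reporting period in Section 10.2.2 and Section 10.2.2.1 was not available in the copy read. Text there could add procedure, but it would still leave an unqualified last bullet to correct.

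**What to change.** Reconcile the passages under one rule, using the exception that the Protocol already contains.

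1. In Section 10.2.2 and the last bullet of Section 10.2.2.1, state that after day 90 an SAE or death judged related to study treatment or a study procedure is still reported as an SAE. For patients under the extension in Section 10.2.1, this lasts until confirmed progression with no further tumour assessments. If the event is learned of later, it is notified as the post-study paragraph describes.
2. State that other deaths after day 90 are documented for survival only. No new duty is needed for late deaths of unknown cause.
3. State that the late related events enter the safety tables of Section 11.3.1.
4. As a minor point, align the subsection on unresolved events with Section 10.2.1 on the follow-up of ongoing SAEs, and say there that investigational product includes FOLFOX, since Table 9 omits it.

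The cost is wording in a few subsections and a few more SAE forms. Reported SAE rates may rise slightly.

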#### **10.2.3. Other events requiring reporting**

##### **10.2.3.1. Overdose**

An overdose is defined as a subject receiving a dose of durvalumab + tremelimumab in excess of that specified in the Investigator's Brochure, unless otherwise specified in this protocol.

Any overdose of a study subject with durvalumab + tremelimumab, with or without associated AEs/SAEs, is required to be reported within 24 hours of knowledge of the event to the sponsor and AstraZeneca/MedImmune Patient Safety or designee using the designated Safety e-mailbox (see Section 10.3.2 for contact information). If the overdose results in an AE, the AE must also be recorded as an AE (see Section 10.3). Overdose does not automatically make an AE serious, but if the consequences of the overdose are serious, for example death or hospitalization, the event is serious and must be recorded and reported as an SAE (see Section 10.3 and Section 10.3.2). There is currently no specific treatment in the event of an overdose of durvalumab or tremelimumab.

The investigator will use clinical judgment to treat any overdose.

##### **10.2.3.2. Hepatic function abnormality**

Hepatic function abnormality (as defined in Section 10.1.3.) in a study subject, with or without associated clinical manifestations, is required to be reported as "hepatic function abnormal" **within 24 hours of knowledge of the event** to the sponsor and AstraZeneca/MedImmune Patient Safety using the designated Safety e-mailbox (see Section 10.3.2 for contact information), unless a definitive underlying diagnosis for the abnormality (e.g., cholelithiasis or bile duct obstruction) that is unrelated to investigational product has been confirmed.

- If the definitive underlying diagnosis for the abnormality has been established and is unrelated to investigational product, the decision to continue dosing of the study subject will be based on the clinical judgment of the investigator.
- If no definitive underlying diagnosis for the abnormality is established, dosing of the study subject must be interrupted immediately. Follow-up investigations and inquiries must be initiated by the investigational site without delay.

Each reported event of hepatic function abnormality will be followed by the investigator and evaluated by the sponsor and AstraZeneca/MedImmune.

#### **10.2.3.3. Pregnancy**

#### **10.2.3.4. Maternal exposure**

If a patient becomes pregnant during the course of the study, the IPs should be discontinued immediately.

Pregnancy itself is not regarded as an AE unless there is a suspicion that the IP under study may have interfered with the effectiveness of a contraceptive medication. Congenital abnormalities or birth defects and spontaneous miscarriages should be reported and handled as SAEs. Elective abortions without complications should not be handled as AEs. The outcome of all pregnancies (spontaneous miscarriage, elective termination, ectopic pregnancy, normal birth, or congenital abnormality) should be followed up and documented even if the patient was discontinued from the study.

If any pregnancy occurs in the course of the study, then the Investigator or other site personnel should inform the appropriate AstraZeneca representatives within 1 day, ie, immediately, but **no later than 24 hours** of when he or she becomes aware of it.

The designated AstraZeneca representative will work with the Investigator to ensure that all relevant information is provided to the AstraZeneca Patient Safety data entry site within 1 to 5 calendar days for SAEs and within 30 days for all other pregnancies.

The same timelines apply when outcome information is available.

#### **10.2.4. Paternal exposure**

Male patients should refrain from fathering a child or donating sperm during the study and for 180 days after the last dose of durvalumab + tremelimumab combination therapy or 90 days after the last dose of durvalumab monotherapy, whichever is the longer time period.

Pregnancy of the patient's partner is not considered to be an AE. However, the outcome of all pregnancies (spontaneous miscarriage, elective termination, ectopic pregnancy, normal birth, or congenital abnormality) occurring from the date of the first dose until 90 days after the last dose should, if possible, be followed up and documented.

Where a report of pregnancy is received, prior to obtaining information about the pregnancy, the Investigator must obtain the consent of the patient's partner. Therefore, the local study team should

adopt the generic ICF template in line with local procedures and submit it to the relevant Ethics Committees (ECs)/Institutional Review Boards (IRBs) prior to use.

## **11. STATISTICAL METHODS AND SAMPLE SIZE DETERMINATION**

### **11.1. Description of analysis sets for the step 1**

Safety and pharmacokinetic analyses will be performed on the first 9 patients. Toxicities during the first 2 cycles will be considered.

